#### Primary outcome measures

We are using the following primary outcome measures based on proportions of:

1. Patients with a history of **peptic ulcer **who have been prescribed a non-selective **NSAID**:

• More specifically, those with a computer-coded diagnosis of peptic ulcer disease, at least six months prior to data collection, who have a computer record for one or more prescriptions for a non-selective NSAID in the six months prior to data collection who have not also had a prescription for a PPI within that six month period

• It should be noted that the denominator for this outcome measure is patients with a computer-coded diagnosis of peptic ulcer disease, at least six months prior to data collection, who have not also had a prescription for a PPI in the six months prior to data collection.

2. Patients with **asthma **who have been prescribed a **beta-blocker**:

• More specifically those with a computer-coded diagnosis of asthma, at least six months prior to data collection, who have a computer record of one or more prescriptions for a beta-blocker (oral preparations or eye drops) in the six months prior to data collection

• The denominator for this outcome measure is patients with a computer-coded diagnosis of asthma, at least six months prior to data collection.

3. Patients **aged 75 years and older **who have been prescribed an **ACE inhibitor or a loop diuretic **long-term (see below) who have not had a computer-recorded check of their renal function and electrolytes in the previous 15 months:

• More specifically, long-term prescribing implies a first prescription for an ACE inhibitor or a loop diuretic at least 15 months before the time of data collection and at least one prescription in the six months beforehand

• The denominator for this outcome measure is patients aged 75 years and older who have been prescribed an ACE inhibitor or a loop diuretic long-term according to the above definition.

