Following this initial meeting, the pharmacists were expected to use a range of techniques to help correct the medication errors that had been identified and prevent future medication errors. They were expected to work closely with the practice team member assigned to provide liaison with other members of the practice.

We envisaged that the pharmacists would be taking any, or all, of the following approaches to deal with patients identified to be at risk from potentially hazardous prescribing and medicines management:

• Inviting patients into the surgery for a prescription review with the pharmacist, or a member of the general practice team, with the aim of correcting medication errors, e.g.

- For patients with a past history of peptic ulcer who were being prescribed a non-selective NSAID to either:

▪ Stop the NSAID

▪ Add a proton pump inhibitor (PPI)

▪ Consider using a COX-2 inhibitor, while recognising concerns about these drugs in relation to cardiovascular risk.

- For patients with asthma who were being prescribed a beta-blocker:

▪ In those taking beta-blocker eye drops for glaucoma, to change to an alternative preparation

▪ In those taking oral beta-blockers, to carefully consider the risks and benefits of the medication and, where appropriate, slowly withdraw the drug and replace it with an alternative preparation.

- For patients who were being prescribed methotrexate without instructions that it should be taken weekly:

▪ Carefully check the dosage instructions

▪ Convey this information to the patient verbally and in writing

▪ Ensure that accurate dosage instructions were entered onto the computer system so that these would be printed out when the drug was next issued.

• Inviting the following groups of patients to have a blood test:

- Those aged 75 years and older being prescribed ACE inhibitors or loop diuretics who had not had a blood test to check renal function and electrolytes within the previous 15 months

- Those being prescribed methotrexate who had not had a full blood count or liver function test within the previous three months

- Those being prescribed warfarin who had not had an INR test within the previous 12 weeks (this is the maximum interval recommended by the British National Formulary[23]).

We envisaged the pharmacists taking the following approaches to try to *prevent *future instances of hazardous prescribing and medicines management, having agreed these approaches with the practice teams:

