### Statistical analysis

Data analysis, using the following analysis plan, will be undertaken blind to treatment arm allocation (i.e. the treatments will be identified only as A and B until analysis is complete). The primary analysis for the clinical outcomes used in the trial will be undertaken using the six-month follow-up data.

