#### Describing baseline prevalence of medication-related problems

The following will be described using the numerator, denominator and percentage by treatment arm, at patient level:

i) Primary outcome measures:

Patients with a history of peptic ulcer prescribed an NSAID without a PPI (numerator)/

Patients with a history of peptic ulcer without a PPI (denominator)

Patients with asthma prescribed a beta-blocker (numerator)/Patients with asthma (denominator)

Patients aged ≥75 on long term ACE inhibitors or diuretics without urea and electrolyte monitoring in the previous 15 months (numerator)/

Patients aged ≥75 on long term ACE inhibitors or diuretics (denominator)

ii) Secondary outcome measures:

Patients with asthma and not CHD prescribed a beta-blocker (numerator)/

Patients with asthma and not CHD (denominator)

Female patients with a history of venous or arterial thromboembolism and arterial thrombosis prescribed combined oral contraceptives (numerator)/

Female patients with a history of venous or arterial thromboembolism and arterial thrombosis (denominator)

Patients prescribed methotrexate for ≥ three months without a full blood count in last three months (numerator)/

Patients prescribed methotrexate for ≥ three months (denominator)

Patients prescribed methotrexate for ≥ three months without an liver function test in last three months (numerator)/

Patients prescribed methotrexate for ≥ three months (denominator)

Patients prescribed warfarin for ≥ three months without an INR in last three months (numerator)/

Patients prescribed warfarin for ≥ three months (denominator)

Patients prescribed lithium for ≥ three months without a lithium level in last three months (numerator)/

Patients prescribed lithium for ≥ three months (denominator)

Patients prescribed amiodarone for ≥ six months without a thyroid function test in the last six months (numerator)/

Patients prescribed amiodarone for ≥ three months (denominator)

Patients prescribed methotrexate without instructions to take weekly (numerator)/

Patients prescribed methotrexate (denominator)

Patients prescribed amiodarone for ≥ one month at a dose >200 mg/day (numerator)/

Patients prescribed amiodarone for ≥ one month (denominator)

Four composite outcome measures will also be used comprising:

Number of patients with at least one prescribing problem (numerator)/

Number of patients at risk of at least one prescribing problem (denominator)

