### Comparisons between treatment arms

All outcome measures are binary in nature. They will be compared between treatment arms using random effects logistic regression with patient at level one and practice at level two. Odds ratios and 95% confidence intervals will be estimated using two-level random intercepts logistic models, with patients at level one and practices at level two. Models will include randomisation stratum as a fixed effect[39]. Three separate analyses will be undertaken [40-42]:

i) adjusting only for stratum (practice level)

ii) adjusting for stratum (practice level) and for the presence of medication-related problems at baseline (patient level).

iii) adjusting for stratum (practice level), baseline medication-related problems (patient level), and deprivation and training status (practice level).

An intention-to-treat analysis will be used such that practices will be analysed in the arms they were allocated to regardless of whether they received the intervention or not[43,44]. Significance will be assessed based on likelihood ratio tests with a p value of < 0.05 taken as significant. Analyses will be undertaken using Stata version 10[45]. Regression models adjusted for stratum and baseline medication problem rates will yield estimates of the cluster and residual variance components, enabling the ICCs to be calculated [45].

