#### Primary outcomes

The proportions of "at risk" patients in each treatment arm with the errors of interest will be compared between treatment arms at six and 12 months after the end of the intervention period in each practice.

The ICC and 95% confidence interval will be estimated for each of the primary outcome measures from the regression models adjusted for stratum and baseline medication errors.

If any practices are lost to follow up, a sensitivity analysis will be undertaken replacing the missing follow up data with the baseline data for that practice[43,44].

It should be noted that some patients (for both primary and secondary outcome measures) will become "at risk" between the time of the baseline data collection and the follow up data collections. For the primary outcome measures this may occur because:

• They have a diagnosis of asthma or peptic ulcer recorded on the computer following the time of the baseline data collection

• They reach the age of 75 years following the time of the baseline data collection

• At time of the baseline data collection, they do not fall within our definition of being prescribed an ACE inhibitor or a loop diuretic long-term, but they do so at the six and/or 12 month follow up data collection points

• They join the practice after the time of baseline data collection and fall within one of the "at risk" groups.

We believe that it is important to include these patients in the analysis because the intervention is aimed not only at correcting hazardous prescribing, but also at introducing systems to prevent future errors. Nevertheless, for the primary outcome measures, sensitivity analysis will be undertaken excluding patients that (for the reasons outlined above) become "at risk" between the baseline data collection and the follow up data collections.

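### Outcome 1 re-forms its denominator after randomisation on PPI use, itself a listed correction, so the baseline-adjusted analyses can be biased in either direction

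*Protocol article*

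**What the plan says.** Under Primary outcome measures, the outcome 1 numerator is ulcer patients prescribed a non-selective NSAID "who have not also had a prescription for a PPI within that six month period". The denominator carries the same condition: ulcer patients "who have not also had a prescription for a PPI in the six months prior to data collection". The section on baseline prevalence repeats it: "Patients with a history of peptic ulcer without a PPI (denominator".

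Outcomes are collected six and 12 months after the 12-week intervention period, and the primary analysis "will be undertaken using the six-month follow-up data". The no-PPI condition is therefore applied afresh at each follow-up.

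Under Pharmacist intervention, one of three listed responses to this error is "Add a proton pump inhibitor (PPI".

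The comparison uses "random effects logistic regression with patient at level one and practice at level two". Model (i) adjusts for stratum only. Model (ii) is described as "adjusting for stratum (practice level) and for the presence of medication-related problems at baseline (patient level", and model (iii) adds deprivation and training status. For changes in the at-risk group, the Primary outcomes section states that "sensitivity analysis will be undertaken excluding patients that (for the reasons outlined above) become 'at risk" after baseline. That covers patients who enter the group, not those who leave it.

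**The concern.** PPI use at follow-up arises after randomisation and can be changed by the intervention. Two listed ways of correcting the same error are scored differently. Stopping the NSAID without a PPI leaves the patient in the data as a non-error. Adding a PPI that is still being issued at follow-up removes the patient's row. Outcome 2 does not have this feature, because its denominator is the diagnosis alone.

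Models (ii) and (iii) compare patients with the same baseline error status. Among those in error at baseline, the arms are then compared on whoever was not corrected by a PPI. If the PPI share of corrections differs by arm, the odds ratio changes even when the true effect does not. The sensitivity analysis limited to patients already at risk at baseline has the same gap. A baseline-adjusted result for this primary outcome could not then be separated from the way practices chose to correct the error.

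**Working it through.** **Inputs from the article (Table 2, outcome 1).** Baseline rate 5.76%; planned rates 5.13% (feedback) and 2.88% (pharmacist); ICC 0.01082; cluster size 63; 64 practices required.

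**Assumed, because the article gives no values.** The share of corrections made by a PPI in each arm; the share of baseline errors that persist; the share of NSAID-free ulcer patients who start a PPI. The model (ii) check uses a closed group of baseline at-risk patients and expected counts, without the practice random effect.

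**1. The plan's own figure.** The two-proportion formula (pooled variance under the null, no continuity correction, two-sided 5%, 80% power) for 5.13% and 2.88% gives 1191 patients per arm. The design effect is 1 + 62 × 0.01082 = 1.671. Then 1191 × 1.671 / 63 = 31.6, so 32 practices per arm and 64 in total, as stated. Power with 34 per arm is 82.8%.

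**2. Model (i), stratum only.** With error reduction r, PPI share of corrections s, and share q of NSAID-free patients starting a PPI:

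rate = E / (E + N), where E = 0.0576(1 − r) and N = 0.9424(1 − q) + 0.0576 r(1 − s).

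- No PPI corrections: 2.88% and 5.13%, OR 0.55.
- All corrections in both arms by PPI: pharmacist 0.0288 / 0.9712 = 2.97%, feedback 5.16%, OR 0.56, power 79.9%.
- All pharmacist-arm and no feedback-arm corrections by PPI: 2.97% and 5.13%, OR 0.57, power 78.9%.
- NSAID-free patients in the pharmacist arm also start PPIs (PPI share 50% in both arms, with the persistence of step 3): at q = 10% the odds are 0.0288 / 0.8580 and 0.0513 / 0.9401, OR 0.62. At q = 20% the OR is 0.69.

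**3. Model (ii), adjusted for baseline error.** Per 10,000 at-risk patients in each arm, 576 are in error at baseline. Assume 70% (feedback) and 30% (pharmacist) of these errors persist.

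- Feedback: 403.2 persist and 172.8 are corrected. New errors are 513 − 403.2 = 109.8.
- Pharmacist: 172.8 persist and 403.2 are corrected. New errors are 288 − 172.8 = 115.2.

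Within the baseline-error group the true OR is (172.8/403.2) / (403.2/172.8) = 0.184. Removing PPI-corrected patients multiplies it by (1 − s_feedback) / (1 − s_pharmacist). A logistic model with arm and baseline error, fitted to all cells, gives:

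| PPI share, feedback | PPI share, pharmacist | OR among baseline errors | Model (ii) OR |
|---|---|---|---|
| corrected patients kept | corrected patients kept | 0.18 | 0.40 |
| 50% | 50% | 0.18 | 0.48 |
| 50% | 80% | 0.46 | 0.78 |
| 50% | 95% | 1.84 | 1.19 |
| 80% | 50% | 0.07 | 0.38 |
| 80% | 30% | 0.05 | 0.30 |

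With equal shares the OR among baseline errors is unchanged. The move to 0.48 comes from reweighting that group against patients without a baseline error, whose OR here is 1.05.

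**4. Dependence on persistence.** The 30% assumption implies that the pharmacist arm prevents no new errors (115.2 against 109.8). With 40% persistence there and the same totals, new errors fall to 288 − 230.4 = 57.6 (OR 0.52 among patients without a baseline error). Model (ii) is then 0.35 with corrected patients kept, 0.38 at equal 50% shares, 0.60 at 50% feedback and 80% pharmacist, and 0.87 at 50% and 95%.

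**The case against.** The denominator is deliberate and consistent. The article draws attention to it, and the planning rate and ICC were estimated with PPI recipients excluded because a PPI protects against the NSAID risk. It is a coherent measure of the population still exposed. Model (i) is almost unaffected, and none of the three models is named as primary. Adding a PPI is listed only for patients who are on an NSAID, so wider PPI starts are assumed. Feedback practices also receive the patient list and educational material and may add PPIs themselves. Replacing a pre-specified primary measure after the interventions were delivered has its own cost.

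Most of this stands, and it rules out several stronger readings that a reader might infer:

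- **That PPI corrections are ignored.** They also leave the numerator, so the error proportion still falls. In model (i) they are slightly under-credited (2.97% instead of 2.88%).
- **That every PPI correction is affected.** Only those with a prescription in the six months before data collection are. A PPI issued during the 12 weeks and not repeated can fall outside that window.
- **That the bias runs against the pharmacist arm.** In models (ii) and (iii) the direction depends on the PPI shares. With 80% feedback and 30% pharmacist, the benefit is exaggerated.
- **That the effect would be reversed.** The 1.19 needs a 95% share in the pharmacist arm and no prevention of new errors. With 40% persistence the same shares give 0.87.

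The objection does not remove the selection itself. Intent behind a denominator does not make it independent of treatment, and no stated analysis restores the patients who leave.

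**Conclusion.** The concern holds as a structural weakness of outcome 1, with limited consequences for one model and indeterminate consequences for the others. The stratum-only comparison stays at an OR of about 0.55 to 0.57, and power with 34 practices per arm falls from about 83% to 79–80% at worst, unless the intervention also puts NSAID-free ulcer patients on PPIs. Models (ii) and (iii) and the baseline-cohort sensitivity analysis can be biased either way: 0.30 to 0.78 around 0.40 in the scenarios shown, with reversal only under extreme assumptions. These ranges rest on assumed persistence and PPI shares and show what is possible, not what is expected. The definition of the denominator and its interaction with a listed correction are read directly from the article and need no assumption. An added analysis is a cheap improvement, and quantitative analysis had not been undertaken when the article was submitted.

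**What to change.** Before unblinding, pre-specify an analysis of outcome 1 whose denominator is all patients with a peptic ulcer code at least six months before data collection, whatever their PPI use. Keep the numerator unchanged (non-selective NSAID, no PPI). Apply it at baseline, six and 12 months, in all three models and in the baseline-cohort analysis. Report it beside the PPI-restricted measure, preferably as the main analysis and at minimum as a sensitivity analysis. Base any baseline-adjusted conclusion for outcome 1 on it. Record the date and reason for the change.

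Costs:

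- The patient-level models need linked rows for PPI-treated ulcer patients at each time point. The article does not say whether these were extracted, so searches may have to be re-run. An extra count per practice would not be enough.
- The percentages will be smaller and less comparable with the pilot rate.
- The rate, ICC and cluster size in Table 2 exclude PPI recipients and do not carry over directly. Power on the new denominator needs re-estimating and should not be assumed unchanged.

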#### Secondary outcome measures

We are collecting data on a number of secondary outcome measures relating to contraindicated prescribing, inadequate monitoring and dosing problems.

#### Contraindicated prescribing

4. Proportions of women with a past medical history of **venous or arterial thrombosis **who have been prescribed the **combined oral contraceptive pill**

• More specifically, women with a history of venous or arterial thrombosis recorded at least six months prior to data collection who have a computer-recorded prescription for the combined oral contraceptive pill in the six months prior to data collection.

#### Inadequate monitoring

These outcomes are based on proportions of:

5. Patients receiving **methotrexate **for at least three months who have not had a recorded full blood count and/or liver function test within the previous three months

• More specifically

5a: patients with one or more prescriptions for methotrexate recorded on computer three to six months prior to data collection *and *in the three months prior to data collection who have not had a computer-recorded full blood count within the previous three months

5b: patients with one or more prescriptions for methotrexate recorded on computer three to six months prior to data collection *and *in the three months prior to data collection who have not had a computer-recorded liver function test within the previous three months.

6. Patients receiving **warfarin **for at least three months who have not had a recorded check of their INR within the previous 12 weeks

• More specifically, patients with one or more prescriptions for warfarin recorded on computer three to six months prior to data collection *and *in the three months prior to data collection who have not had a computer-recorded INR within the previous three months.

7. Patients receiving **lithium **for at least three months who have not had a recorded check of their lithium levels within the previous three months

• More specifically, patients with one or more prescriptions for lithium recorded on computer three to six months prior to data collection *and *in the three months prior to data collection who have not had a computer-recorded lithium level within the previous three months.

8. Patients receiving **amiodarone **for at least six months who have not had a thyroid function test within the previous six months

• More specifically, patients with one or more prescriptions for amiodarone recorded on computer 6–12 months prior to data collection and in the three months prior to data collection who have not had a computer-recorded thyroid function test within the previous six months.

#### Dosing problems

These outcomes are based on proportions of:

9. Patients receiving prescriptions of **methotrexate **without instructions that the drug should be taken **weekly**.

• More specifically, patients with one or more prescriptions for methotrexate recorded on computer within the three months prior to data collection who do not have the term "weekly" or "week" in the dosage instructions field of the latest prescription for the drug.

10. Patients receiving prescriptions of **amiodarone **for at least one month who are receiving a dose of more than 200 mg per day

• More specifically, patients with evidence of being prescribed amiodarone 200 mg tablets for more than one month in the three months prior to data collection, who do not have the term "once daily" (or similar) in the dosage instructions field for the drug.

#### Additional outcome measure relating to prescription of beta-blockers to patients with asthma

This secondary outcome measure is based on proportions of patients with **asthma **who do **not **have coronary heart disease (CHD) and have been prescribed a **beta-blocker**:

• More specifically those with a computer-coded diagnosis of asthma and no record of CHD, at least six months prior to data collection, who have a computer record of one or more prescriptions for a beta-blocker (oral preparations or eye drops) in the six months prior to data collection

• The denominator for this outcome measure is patients with a computer-coded diagnosis of asthma and no computer-coded record of CHD, at least six months prior to data collection.

